**Figure 4 fig4:**
[figure not shown]
Symbolic depiction of anticipated group differences and interindividual variance in the magnitude of nocebo effects induced by negative instructions and experience (group Neg-Neg), negative instructions and unaltered pain experience (group Neg-Con), control instructions and negative experience (group Con-Neg) or no expectancy manipulations (group Con-Con) in the four experimental groups.

#### Aim 1: to test dynamic changes in treatment- and pain-related expectations within- and outside of the psychosocial treatment context, i.e., on study days 1 and 2, as mediators of nocebo effects

3.1.1.

Given that negative expectations are at the heart of the experimental design of the NoVis study, the first step will be to interrogate group differences in expectations. This will be achieved based on analyses of three distinct yet complementary measures. Firstly, we will analyze G-EEE scores, providing a novel screening tool capturing prior and current treatment-related experiences and expectations, including not only improvement but also worsening as well as potential side effects (G-EEE) (54). As our experimental manipulations are designed to induce negative expectations as mediators of nocebo effects, we anticipate that analyses will confirm the presence of group differences regarding the expected and/or experienced worsening of symptoms. This should be observable in groups that receive negative instruction regarding possible drug-induced pain amplification as well as in groups experiencing pain amplification, with greatest effects hypothesized to occur in the group with negative instruction combined with a negative experience of amplified pain (i.e., the “Negative–Negative” Group).

Secondly, analyses of the G-EEE scores will be complemented and refined by analyses of VAS assessing expected pain intensity and unpleasantness. We assume that expectancy VAS ratings constitute a more sensitive measure as assessments are accomplished in direct timely proximity to pain stimulation phases, allowing us to interrogate dynamic changes in pain-related expectations before and after different experiences of repeated acute pain stimuli during the pain stimulation phases. VAS also directly target pain-related expectations, which are reportedly highly correlated with perceived pain intensity in placebo/nocebo studies [e.g., (40)]. Since pain expectancy ratings are acquired for each pain modality, analyses will allow insight into possible differences in negative expectations for visceral vs. somatic pain stimuli. Therefore, we regard VAS expectancy results as key manipulations checks. It will be particularly interesting to elucidate possible group differences in the experimental groups that were randomized to a negative pain experience (i.e., surreptitiously increased temperature for somatic pain stimuli) when compared to groups in which objective pain stimulation intensities remain unaltered (i.e., experience control groups). We anticipate that compared to control groups, these negative experience groups will demonstrate greater expected pain intensity prior to the *Test-1 Phase* based on the preceding experience of amplified pain intensity. Although we surreptitiously increase only thermal stimulation intensities, we expect to find effects not only for the somatic pain modality but also for the visceral modality. This assumption is based on the hypothesis that a generalization across pain modalities will take place, possibly due to cognitions relating to allocation to drug rather than placebo in groups that were negatively instructed. In other words, we expect that participants who were informed that there exists a 50% chance of receiving a drug that amplifies pain will interpret their perception of greater thermal pain intensity as evidence that they were randomized into the naloxone group, resulting in immediate nocebo effects also for the visceral modality.

Thirdly, learning to anticipate potential bodily harm is essential for adaptive behavior. Via associative learning, conditioned danger cues generate negative expectations along with anticipatory preparatory psychophysiological responses to impending threat (27). Such learned negative expectations can results in hypervigilance and amplification of pain experience, constituting a key mechanism in the translational framework of nocebo effects. We will therefore analyze behavioral and skin conductance responses to conditioned pain-predictive cues as measures of learned conditioned pain-related fear during pain anticipation. We anticipate group differences in the magnitude of conditioned fear responses, with greatest responses expected in the “Negative–Negative” group. Of note, the behavioral read-out we will implement constitutes changes in emotional valence of pain-predictive cues. Emotional valence is relevant to all types of threat, shapes the perception of aversive stimuli, including pain (78), and drives threat-related behaviors like approach and avoidance (79). It is highly relevant to the specificity of visceral pain (30), and sensitive to modulation by placebo/nocebo mechanisms (27, 32). Prior pain-related fear conditioning studies from our own group [reviewed in (27)] and in the broader fear conditioning literature support the notion that conditioned changes in cue valence constitute a sensitive and relevant behavioral measure capturing the formation, as well as the extinction and return of anticipatory fear responses in healthy adults (80) and clinical populations (79). Most recent evidence supports its sensitivity to nocebo mechanisms (81).

#### Aim 2: to test the effects of negative treatment expectations induced by instruction and/or experience on subjective and objective responses to acute visceral and somatic pain stimuli

3.1.2.

Regarding perceived pain intensity and unpleasantness as main outcomes, we expect that both negative instruction as well as negative experience will result in hyperalgesia for both pain modalities, i.e., greater pain intensity and unpleasantness ratings during the *Test-1 Phase* vs. *Baseline* in experimental groups “Control-Negative” and “Negative-Control” when compared to the group “Control–Control.” Of note, the bars depicting expected results (Figure 4) indicate a similar magnitude of nocebo effect for the groups “Control-Negative” and “Negative-Control.” In other words, we assume in this visualization that the efficacy or impact of instruction and experience will be comparable. It should be stressed, however, that there is no prior evidence testing such an assumption in similar experimental approaches, and it will be interesting to reveal whether the impact of instruction vs. experience is indeed comparable as a basis for translation into practice. If, for example, the impact of negative experience is more “powerful” in terms of inducing sustained nocebo effects when compared to instruction, this will inform strategic and conceptual developments aiming to minimize nocebo effects in clinical practice. Further, we anticipate that the negative experience of objectively increased thermal pain will impact on the perceptual response also to visceral pain (e.g., via generalization and/or cognitive attribution effects, as explained above), exerting an impact also on both pain modalities during the *Test-1 Phase*. Regarding objective measures related to pain, as secondary outcomes, we will explore group differences in psychophysiological responses expecting greater sympathetic activation reflected by differences in HRV and EGG measures in the “Control-Negative” and “Negative-Control” when compared to the group “Control–Control.”

#### Aim 3: to determine if a negative treatment experience enhances the magnitude of negative instruction effects

3.1.3.

This study aim constitutes the most crucial and arguably most clinically relevant aspect of this study with respect to both novelty and putative implications. In clinical reality, negative prior experiences with the same or a similar treatment (context) are very common, especially in patients with chronic symptoms that are difficult to treat, as in DGBI. Therefore, experimentally testing not only the effects of instruction and experience separately but rather their combination is important since the combination of instruction and experience has been shown to be particularly effective in eliciting a nocebo effect (39). We therefore herein anticipate an interaction of these factors, resulting in greatest nocebo effects induced by the combination of negative instruction and negative experience, i.e., in the “Negative–Negative” group, as visualized in Figure 4. The magnitude of the increase in nocebo effect in this group over the “Control-Negative” and “Negative-Control” groups will depend on effect sizes in those groups, which cannot be estimated based on existing data. It is however conceivable that the additional increase will be substantial in case additive or even synergistic effects occur. If this were the case, clinical application of nocebo research would have to target the role of (prior) treatment failure within the context of patient-provider communication in order to avoid or minimize nocebo effects. Given prior evidence of transfer or carry-over effects of prior treatment history to the response to a novel treatment (82), including evidence that the effects of treatment failure generalize across different routes of drug administration (83), the clinical relevance of treatment history (i.e., treatment experience) cannot be underestimated. At the same time, it is also possible that only the combination of instruction and experience will result in a discernable nocebo effect, possibly resulting from small or even absent negative expectations resulting from our experimental manipulations when accomplished separately. It is also conceivable that the study setting involving pain stimuli already contains nocebo mechanisms that impact on the “Control–Control” group as well. The information that painful stimuli from two pain modalities will be delivered, which is obviously given to all experimental groups, may constitute a driver of negative expectations that our additional experimental manipulations must override for us to be able to detect effects. The magnitude of such effects cannot be estimated without additional control groups, especially a group that does not receive any painful stimuli. Hence, it should be noted that the symbolic depiction of the expected magnitude of nocebo effects in Figure 4 as essentially zero in the “Control–Control” group, reflects the concept of the study design rather than the true absence of any negative expectancy effects in this group expecting and experiencing aversive painful stimuli.

#### Aim 4: to compare the magnitude of nocebo effects in the visceral versus the somatic pain modality

3.1.4.

The present study is the first to allow insight into nocebo effects across modalities, aiming to test the notion that effects of negative expectations may be enhanced for the visceral when compared to the somatic modality. This is based on earlier findings supporting a distinct role of fear and stress for perceptual responses to pain arising from the viscera and partially distinct underlying neural circuitry (29, 41). It is therefore intriguing to assume that interoceptive, visceral perceptions may be more modifiable by psychological factors, including negative expectations. Putting this to a test within this comprehensive study, we expect greater and more sustained nocebo effects on visceral vs. somatic pain responses. We anticipate that this will be particularly evident in measures reflecting emotional-motivational facets of pain, which we herein assess with VAS of perceived pain unpleasantness and visceral pain-related fear in response to conditioned predictive cues.

#### Aim 5: to assess the persistence of nocebo effects on responses evoked by a re-exposure to pain stimuli 1 week later

3.1.5.

We expect sustained effects of expectancy manipulations accomplished on study day 1, which we interrogate based on group comparisons of the *Test-2 Phase*, as well as based on analyses of change scores from the *Test-1* Phase to the *Test-2 Phase*. We anticipate that groups with negative instructions and/or negative experience will expect greater pain on study day 2, i.e., prior to the *Test-2 Phase*, even though elements of the treatment context, such as an i.v. line, will not be present on that day. If we indeed can show such effects, this would be an important finding toward explaining how nocebo effects may be maintained in clinical reality over time and repeated symptom experiences. Given our considerations about differences between pain modalities, especially the putatively greater psychological modulation of visceral pain, we expect sustained effects to be enhanced for the visceral pain modality. We will focus on elucidating modality-specific facets of pain recall, aiming to further elucidate the notion of a memory bias for visceral pain, expanding on our previous work (84) and the notion that visceral pain-related fear memories may be particularly resistant to extinction (41).

#### Aim 6: to identify predictors of interindividual variability in the magnitude of nocebo effects and to elucidate associations with state and trait variables relevant to stress, anxiety, and fear at the behavioral, psychophysiological and neuroendocrine levels

3.1.6.

We expect that negative expectation effects are at least in part mediated or moderated by state and trait characteristics reflective of stress, anxiety or fear, and arousal, and will explore this via group comparisons and exploratory correlational and regression analyses. A role of trait or state negative emotions or stress in nocebo effects has been proposed based on experimental evidence that, however, almost exclusively came from research in somatic pain models [reviewed in (27)]. Briefly, studies have suggested a role of dispositional fear and anxiety as well as state anxiety and stress. There also exists first evidence that HPA-axis and sympathetic mediators may play a role in nocebo responses. In visceral pain, existing evidence is inconclusive, with more findings failing to support a role of stress and anxiety than those supporting their contribution, unless stress is experimentally induced or augmented (40). It is also conceivable that the role of stress or stress mediators in the generation and maintenance of nocebo effects has not been consistently detected due to the absence of longer-term or repeated testing, essentially omitting knowledge about memory. Stress and stress mediators demonstrably impact on associative learning and memory processes (84), including conditioned pain-related learning and extinction, which are distinctly altered in patients with IBS (28, 85). Stress may facilitate a reactivation of the pain-related memory trace, exerting an impact on pain-related outcomes that emerge during re-exposure to painful stimuli, herein on study day 2. Given these considerations, the present study assesses a variety of measures reflecting different facets of stress, anxiety, and fear on psychological and neurobiological state and trait levels, which will allow for hypothesis-generating exploratory analyses for hopefully more firm conclusions.

### Strengths and limitations

3.2.

The study “NoVis” has strengths as well as limitations. Strengths include the experimental study design that systematically manipulates negative expectations via instruction and/or experience, thereby testing effects of treatment information via suggestion and effects of learning/conditioning as the two principle psychological mechanisms underlying expectancy effects not only separately, but also in combination. As such, this is the first study addressing the interaction of factors that are known to induce nocebo effects from a translational perspective. This will not only fill gaps in knowledge from a mechanistic perspective, but has also the potential to be of great value for clinical application in terms of preventing or reducing nocebo effects in the treatment of DGBI and other visceral pain conditions. Similar advantages arise from the implementation of interoceptive visceral and exteroceptive somatic pain stimuli within a translational “multiple-threat paradigm.” These paradigms more closely model the experience of multiple symptoms arising from the viscera and other bodily sites, reflecting patients’ clinical reality of experiencing aversive intestinal and extraintestinal symptoms, either as part of the typical clinical phenotypes, such as in inflammatory bowel diseases, or as part of frequent comorbidities between chronic pain conditions. For mechanistic research into psychological mechanisms relevant to understanding the normal and adaptive specificity of pain responses for the visceral modality, these paradigms have proven to be highly instrumental not only in healthy individuals [e.g., (22, 29)] but also in patients (86). Indeed, when repeatedly confronted with visceral and somatic painful stimuli matched to intensity, healthy volunteers perceive visceral stimuli as more unpleasant, fear-evoking, and threatening. Distinct differences are also observable at the level of neural representations of visceral versus somatic pain [e.g., (41, 86)], in line with a proposed greater biological salience of visceral signals which may shape perception and pain-related cognitive and emotional responses, including learning and memory processes underlying nocebo effects. Another strength is the 2-day study paradigm with a re-exposure to the same pain stimuli 7 days after first testing without a treatment, allowing to elucidate longer-term effects and crucial aspects of learning and memory processes, including explicit memories (i.e., reported pain recall and extent of recalled pain area) as well as implicit effects of prior experience (i.e., responses to conditioned cues; expectations regarding pain intensity). The sustainability of nocebo effects over time, especially the impact of a previous negative treatment experience on the response to subsequent exposure to contextual or sensory stimuli cannot be underestimated in terms of their clinical relevance, as illustrated by carry-over effects demonstrated for the somatic pain modality (82, 83). Finally, the combination of subjective and objective measures to capture diverse facets relevant to pain, fear, and stress will allow not only hypothesis-testing but also hypothesis-generating analyses that can broaden the horizon of possible mediators and moderators and that have the potential to further conceptual and methodological advances.

Limitations and potential pitfalls are equally important to consider. Firstly, while all participants are truthfully informed that the purpose of the study is to elucidate psychobiological mechanisms underlying changes in visceral compared to somatic pain perception upon repeated painful experiences, the study procedures of consent form A (i.e., negative instruction groups) involve a deception. To induce negative treatment-related expectations, participants are informed that they have a 50% chance of receiving either a pronociceptive drug or saline, mimicking clinical treatment scenarios characterized by uncertainty regarding symptom worsening or the occurrence of side effects or adverse events, such as in clinical trials. In reality, herein the probability of receiving saline is 100%. The administration of saline and the scientific justification for providing different instructions to experimental groups will be disclosed after the conclusion of the study, at which time participants will have the opportunity to withdraw their data. While a comprehensive discussion of ethical considerations is beyond the scope herein, the use of deception is not unequivocal, requires justification, and rightfully constitutes an issue of critical debate. There exist different solutions, such as open-label placebos [e.g., (87)], with limited applicability for nocebo research, and authorized consent [e.g., (88)]. A comprehensive work focused on ethical considerations specifically pertaining to nocebo effects is provided herein (89). Secondly, while interindividual variability is a highly relevant aspect to consider, it could at the same time hamper the detection of small effects. The sample size with a goal of *N* = 30 per experimental group was determined based on a prior power calculation and is consistent with (or even larger than) similar experimental work on visceral pain modulation [e.g., (40)] and the broader field [reviewed in (90)]. While the inclusion of diverse and complementary secondary outcome measures at different levels (behavioral, psychophysiological, brain) is consistent with sustainability goals in scientific research and will allow exploratory analyses of diverse study aims, multiple tests and comparisons will be accomplished. This comprehensive study protocol provides readers with maximal transparency, however, there is a risk of potential inflation of *p*-values and false positive results, and findings will have to be interpreted with due caution, requiring replication in independent samples and/or settings. Thirdly, normal changes in perceptual responses to repeated visceral vs. somatic stimuli may differ between modalities as well as between individuals, as suggested by our previous work in similar paradigms. Careful calibration and matching accomplished herein to overcome this challenge may not fully prevent this, with a habituation to cutaneous thermal pain stimuli over time constituting the most likely pitfall. This will be quantifiable in the “Control–Control” group, and of course statistically-controlled for, but analyses directly focusing on differences between pain modalities induced by expectancy manipulations will nevertheless have to overcome this variability. As we cannot with certainty exclude that spontaneous changes in perception occurring independent of our expectancy manipulations interfere with their impact in a modality-specific manner, we will conduct initial analyses within each pain modality separately, i.e., without including pain modality as a repeated factor. Dedicated analyses will be accomplished to elucidate differences between modalities, e.g., using delta scores on the modality difference, as previously accomplished [e.g., (41)]. Finally, limitations arise from the fact that the study is conducted in a tightly-screened sample of relatively young healthy adults. We will recruit men and women, offering opportunities to explore effects of sex/gender, especially within predictor analyses (aim 6). Regarding planned group analyses (e.g., for aims 2–4), (sub)sample sizes are likely too small for any firm conclusions regarding effects of sex/gender, yet exploratory analyses can be accomplished and are interesting given that females and males may differ with respect to the generation of expectancies by suggestions and conditioning processes, respectively (91). Mitigating possible gender-related confounding remains a challenge in experimental research, especially in studies involving visceral pain stimuli posing feasibility restrictions for larger samples that would provide adequate statistical power for detecting sex differences. We and others have previously accomplished some dedicated research on this important subject in the context of visceral pain and visceral pain modulation [e.g., (31, 92–94), as recently reviewed in (9)]. Overall, volunteers herein will not be representative of diverse age, cultural, and ethnic groups, and certainly not of vulnerable individuals or even patients with DGBI and multiple comorbidities. As a complex psychosocial phenomenon, expectancy effects in psychosocial treatment contexts are modulated by societal, cultural, and numerous individual factors, which we will only partially be able to capture and interrogate herein. This is particularly relevant for analyses aiming to address the putative contribution of trait- and state measures relevant to stress and anxiety. While it is tempting to speculate that interactions between stress and negative expectancy effects — whether induced by suggestions or conditioning—could be increased in patients, the translation from healthy individuals tested in experimental laboratory settings to clinical populations is far from unequivocal. Clearly, it is a challenging yet indispensable future research task to elucidate mediators and moderators of placebo and nocebo responses in patients experiencing chronic visceral pain in order to delineate the putative role of stress in nocebo effects in laboratory research, everyday clinical practice as well as in clinical trials.

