### Design and outcomes

2.2.

The study design is visualized in Figure 1, and procedures are described in detail in subsequent sections. The overall idea behind the design is to experimentally create negative treatment expectations through instruction and experience within a treatment context. This is reflected by the key elements of the repeated measures between-subject design containing the between-group factors “treatment instruction” (negative vs. control instruction) and “treatment experience” (negative vs. control experience). To assess the impact of experimental manipulations on outcome measures, subjective and objective responses to a series of visceral and somatic pain stimuli, delivered during several pain stimulation phases, are assessed (repeated factor). Healthy volunteers are randomized into four experimental groups (recruitment goal: *N* = 30 per group). On study day 1, pain thresholding and calibration/matching procedures and a brief pain habituation phase are initially accomplished. This is done to identify individual stimulation intensities for the pain stimulation phases. Several pain stimulation phases are subsequently accomplished (i.e., three on study day 1; one on study day 2), all consisting of a series of individually-calibrated rectal and thermal pain stimuli. After a *Baseline Phase*, all participants receive an i.v. catheter as a salient element of the psychosocial treatment context, with distinct treatment instructions. Briefly, the negative treatment instruction groups are informed that the opioid antagonist naloxone, which amplifies pain, or saline may be administered in a double-blinded manner. Instruction control groups are informed that only saline is administered as part of standardized procedures. In the subsequent *Experience Phase*, thermal pain stimulation intensities are surreptitiously increased in the negative experience groups to create a clearly discernable experience of amplified pain, whereas intensities remain unaltered in the experience control groups. Two *Test Phases* are accomplished, comprising the identical pain stimulation intensities as during *Baseline*. To test short-term effects of expectancy manipulations, the first test phase is accomplished on study day 1 (*Test-1 Phase*). To explore the persistence of effects, another test phase is accomplished 1 week later (*Test-2 Phase*), yet without any of the salient elements of the treatment context (i.e., there is no i.v. and no interaction with the study physician). In all pain stimulation phases, different facets of visceral and somatic pain perception are acquired, along with questionnaires and ratings, psychophysiological recordings, and saliva and blood sampling at various time points (see section 2.5 for details on measures). Note that in order to minimize circadian effects, all experimental testing is accomplished between 13:00 and 17:00 h, with identical starting times for study day 1 and 2 for each participant. Participants are instructed to abstain from physical exercise on the study day, and to omit food and drink (other than water) within 90 min of the scheduled arrival to the laboratory. They are also instructed not to apply body lotion on the abdomen given application of electrodes on the skin.

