### Equipment

2.3.

For the application of phasic visceral pain stimuli, pressure-controlled rectal distensions are delivered using a barostat system (Distender Series II™, 1,300 mL Single Balloon Barostat, G&J Electronics, Toronto, ON, Canada). For the application of phasic somatic pain stimuli, cutaneous thermal stimuli are applied on the skin of the left lower abdomen using a thermode (PATHWAY model CHEPS; Medoc Ltd., Advanced Medical Systems, Ramat Yishai, Israel). For presentation of visual stimuli (i.e., pain-predictive cues) and for digitized online ratings, a commercially available stimulus delivery and experimental control software (Presentation^®^, Neurobehavioral Systems, Albany, CA, United States) is used. For psychophysiological responses, i.e., electrodermal activity (EDA), heart rate variability (HRV), and electrogastrography (EGG) recordings, a commercially available system (BIOPAC MP160 system, Biopac Systems, Inc. Goleta, CA, United States with AcqKnowledge^®^ 5.0.1. software) is used.

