#### Treatment experience

2.4.4.

To induce different treatment experiences, in the groups randomized to a negative treatment experience the somatic pain stimulus intensity (i.e., temperature of the thermode) is surreptitiously increased to the pre-calibrated VAS 80 mm target, whereas it remains unchanged in groups randomized to a neutral treatment experience (control groups). Note that rectal distension pressures, preselected to induce moderately painful visceral pain (VAS 50 mm), the objective intensity (i.e., the distension pressure) remains unchanged in all groups. This is done based on conceptual considerations (see section 4, aim 1), including the more precise nature of somatic pain perception and the assumption that generalization effects will occur.

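### Somatic contrasts between negative-experience and control-experience groups combine expectation with any carry-over from the hotter stimuli, which the Control–Control group cannot capture

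*Protocol article*

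**What the plan says.** Section 3.2 (Strengths and limitations) observes that "normal changes in perceptual responses to repeated visceral vs. somatic stimuli may differ between modalities as well as between individuals", "with a habituation to cutaneous thermal pain stimuli over time constituting the most likely pitfall. This will be quantifiable in the" Control–Control group. The sentence goes on to say that this drift will also be controlled for statistically.

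Section 2.4.4 (Treatment experience) describes what happens between Baseline and Test-1. In the negative-experience groups the thermode temperature is "surreptitiously increased to the pre-calibrated VAS 80 mm target, whereas it remains unchanged in groups randomized to a neutral treatment experience". Section 2.2 agrees for the other arms: "whereas intensities remain unaltered in the experience control groups". The Figure 1 legend assigns the hotter stimuli to Neg-Neg and Con-Neg, and unaltered stimuli to Neg-Con and Con-Con. Rectal pressure is the same in all four groups (2.4.4). Section 2.3 gives one thermal region: "cutaneous thermal stimuli are applied on the skin of the left lower abdomen".

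The primary outcome is change from Baseline to Test-1 within each modality (2.2). For Aim 2 (3.1.2) the authors write "we expect that both negative instruction as well as negative experience will result in hyperalgesia for both pain modalities", judged by comparing Con-Neg and Neg-Con with Con-Con. The same section wants to learn whether instruction or experience has the stronger impact. Aim 4 compares modalities through visceral-minus-somatic delta scores (2.2).

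**The concern.** Con-Neg and Con-Con differ in two ways when Test-1 begins. Con-Neg may expect more pain, and its skin has also received hotter stimuli that Con-Con did not receive in that phase. Returning from a VAS 80 mm stimulus to a VAS 50 mm stimulus can change a rating through sensitisation, altered habituation or contrast, with no change in expectation.

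At stake is the meaning of a primary result. A somatic difference between Con-Neg and Con-Con would be reported as nocebo hyperalgesia although part or all of it could be physical or perceptual. Sensitisation would inflate the apparent effect; habituation or contrast would hide a real one. Ranking instruction against experience in the somatic modality is affected as well, because only the experience arms carry this extra term.

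**Working it through.** **Plan's own figure.** The article gives no number for habituation or carry-over. The nearest figure, N = 96 (2.1), is not in dispute. With f = d/2 = 0.2, four groups, two phases and an assumed correlation of 0.5, λ = 0.2² × 96 × 2 / (1 − 0.5) = 15.36 on 3 and 92 degrees of freedom. Power is 0.91, and N = 96 is reproduced.

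**Model for the somatic change score (Test-1 minus Baseline).** Let h be spontaneous drift, i the instruction effect, e the expectation effect of experience, ie their interaction, and c the carry-over of hotter stimulation, taken as additive.

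- Con-Con = h
- Neg-Con = h + i
- Con-Neg = h + e + c
- Neg-Neg = h + i + e + ie + c

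**Contrasts.**

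| Somatic contrast | Result | Contains c? |
|---|---|---|
| Neg-Con − Con-Con | i | no |
| Con-Neg − Con-Con | e + c | yes |
| Neg-Neg − Con-Con | i + e + ie + c | yes |
| Neg-Neg − Neg-Con | e + ie + c | yes |
| Experience main effect | e + ie/2 + c | yes |
| Con-Neg − Neg-Con (experience vs instruction) | e + c − i | yes |
| Neg-Neg − Con-Neg | i + ie | no |
| Interaction | ie | no |

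Drift h cancels in every row. Carry-over c remains wherever a hotter-stimulus arm is set against an unaltered arm. No arm receives the hotter stimuli without the experience manipulation, so c cannot be isolated.

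**Aim 4.** With subscripts v and s for visceral and somatic, the delta in Con-Neg relative to Con-Con is (e_v) − (e_s + c) = (e_v − e_s) − c. A negative c (habituation or contrast) would mimic the larger visceral effect that the authors predict; a positive c would mask it.

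**If c is not additive.** If c differs by instruction (c_N with negative instruction, c_C without), the interaction becomes ie + (c_N − c_C), and its protection is lost.

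**Illustration only.** The document gives no value for c. Suppose there is no true nocebo effect and c is a given fraction of the SD of the somatic change score. Two-sided 5% t-tests have noncentrality c√(30/2) for Con-Neg vs Con-Con and c√(60/2) for the experience main effect.

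| Assumed c (SD) | Con-Neg vs Con-Con, 30 vs 30 | Experience main effect, 60 vs 60 |
|---|---|---|
| 0.2 | 12% | 19% |
| 0.4 | 33% | 58% |
| 0.5 | 48% | 78% |
| 0.8 | 86% | 99% |

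Conversely, an expectation effect of 0.4 SD with c = −0.4 SD gives an expected difference of zero.

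**The case against.** Section 3.2 speaks of normal, spontaneous change. Con-Con does measure that, and the algebra shows it cancels in every comparison with Con-Con. This stands. A reader might infer that the habituation statement is wrong for half the sample; it is not. It is silent about a different quantity.

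A reader might also infer that Con-Con participants never meet the VAS 80 mm level. All groups undergo the same calibration, in which that level is determined (2.4.1 and the Figure 1 legend). This precedes Baseline and is common to all arms, so it does not repair the later contrast.

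The details that would govern the size of carry-over are not stated. The count of six stimuli per modality is given for Baseline, Test-1 and Test-2 (2.4.2), not expressly for the Experience Phase. The interval before Test-1 is not given, and saliva sampling, a state questionnaire and a blood draw fall between the phases (2.5.4). Repositioning of the thermode within the region is not described. A condensed article may leave these to the full protocol. No size can therefore be claimed. Nor can the planned d = 0.4 serve as a yardstick for carry-over: it is stated for an interaction, not for a pairwise difference, and no SD of change is given.

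Other planned elements help only in part. Expectation ratings before each phase and mediation analyses (2.2, 2.5.2) show whether expectation moved, but hotter stimulation can move expectation and later ratings by separate routes. Test-2, a week later, is further from the hotter stimuli but is not the primary contrast. Separate analyses by modality keep the somatic carry-over out of the visceral results; they do not remove it from the somatic ones.

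Finally, randomisation makes Con-Neg vs Con-Con a fair estimate of the total effect of the experience manipulation. That is true; what fails is attributing the total to expectation.

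**Conclusion.** The concern holds as a limit on interpretation. In the somatic modality, four results (Con-Neg vs Con-Con, Neg-Neg vs Con-Con, Neg-Neg vs Neg-Con and the experience main effect) combine expectation with any carry-over from the hotter stimuli. The Aim 4 delta in the negative-experience groups inherits the same term with reversed sign. The separation fails because of the arm structure, whatever value carry-over takes. Its size and direction cannot be estimated from the document, and the rejection rates above only illustrate assumed values.

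A reader might infer that the study's central question, Aim 3, is undermined. The document does not support that: under additive carry-over the interaction and Neg-Neg vs Con-Neg are unaffected. Neg-Con vs Con-Con is unaffected in any case. The visceral contrasts have equal distension pressure in all arms. Attributing them to expectation still assumes that hotter skin stimulation does not itself alter rectal perception by another route.

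**What to change.** Change the text as follows.

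- **3.2:** add that Con-Con controls spontaneous drift but not carry-over from the hotter thermal stimuli given to Con-Neg and Neg-Neg.
- **2.2 and 3.1.2:** report the four somatic experience contrasts as the combined effect of expectation and prior hotter stimulation, and do not use them to rank instruction against experience.
- **Somatic nocebo claims:** rest them on contrasts with equal thermal exposure: Neg-Con vs Con-Con, Neg-Neg vs Con-Neg, and the interaction, stating the additivity assumption.
- **Experience-induced nocebo effect:** attribute it to expectation on the visceral data.
- **Aim 4 (2.2 and 3.1.4):** attach the same caution to the delta in the negative-experience groups.

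No new data, arm or test hierarchy is needed. The cost is that the somatic experience contrasts and the Aim 4 delta in those groups lose a pure nocebo interpretation.
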